### Study endpoints

The primary endpoint is MSI measured by CMR at 1 week after the index PPCI. The secondary endpoints are the peak time of CK-MB and TnI/TnT after PPCI; the postoperative fall time of the ST segment on ECG; the rate of plasma LDL-C compliance (< 1.4 mmol/L and a reduction of >50% from baseline) at 1, 3, and 6 months after PPCI; infarct size and EF measured by CMR at 6 months after PPCI; the occurrence of MACE.

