### Interventions and follow-up

After grouping, enrolled patients will undergo PPCI with new-generation drug-eluting stents. Immediately after PPCI, patients grouped in the PCSK9 inhibitor group will be injected with alirocumab subcutaneously at a dose of 75 mg after the PPCI, followed by injections at the same dose every 2 weeks for 3 months on the basis of conventional treatment. Patients in the control group will receive conventional treatment in accordance with the published guidelines, including dual anti-platelet therapy and statins (15). Patients will be evaluated at 1 week and at 1, 3, and 6 months after the index PPCI, and the occurrence of clinical events will be monitored. As the primary endpoint, the MSI will be measured by CMR at 1 week after PPCI. As the key secondary endpoints, the infarct size and ejection fraction (EF) will also be measured by CMR at 6 months after PPCI. Additionally, the peak time of creatine kinase (CK)-MB and troponin I (TnI)/TnT, as well as the postoperative fall time of the ST segment on electrocardiography (ECG) will be recorded. Plasma LDL-C compliance rate (< 1.4 mmol/L and reduction >50% of baseline) and the occurrence of major adverse cardiovascular event (MACE: a composite of cardiovascular death, non-fatal myocardial infarction, stent thrombosis, repeat revascularization, stroke, and heart failure needed to be hospitalized) will be recorded at 1, 3, and 6 months after PPCI (16). Besides, medications at discharge will be recorded, especially those that affect cardiac remodeling. The investigators will follow up with the patients by office visits or telephone contact. The data collected during all follow-ups will be submitted to the original documents. If any patient is admitted to a non-research hospital again, every effort will be made to obtain the original data from the hospital. For all re-infarctions, ECG and myocardial enzyme data will be obtained and recorded. The following events will lead to termination of the patient's follow-up: (1) death; (2) voluntary withdrawal; (3) evacuation of patients by the investigators based on clinical manifestations; and (4) loss to follow-up (informal withdrawal). The follow-up schedule is shown in Figure 1 and Table 2.

**Table 2 T2:** Timetable of activities planned during the study.

**Time point**	**Before operation**	**Follow-up**			
		**1 week**	**1 month (±10 days)**	**3 months (±20 days)**	**6 months (±20 days)**
Informed consent	×				

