### Sample size calculation

Referring to our prior small sample size study, the MSI was higher in the PCSK9 inhibitor group (mean: 0.50; standard deviation [SD]: 0.16) than in the control group (mean: 0.41; SD: 0.15). To guarantee 90% power of the study at a significance level of 0.05, at least 64 patients per group will be needed. Considering a dropout rate of 20%, the required sample size is 160 (80 patients in each group). PASS 15 was used to calculate the sample size.

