### Statistical analysis

Continuous variables (including the primary endpoint) will be expressed as mean (SD) or median (interquartile rage) and will be compared using the *t*-test or the Mann-Whitney *U* test, as appropriate. Categorical variables will be expressed as counts and percentages and compared using the χ2 test or Fisher's exact test, as appropriate. We plan to assess the consistency of the treatment effect on the primary endpoint among three pre-specified subgroups that will be analyzed individually and then in a multivariate model. The following subgroup analyses are planned: age: < 60 years vs. ≥60 years; sex: female vs. male; duration from symptom onset to study drug infusion: < 3 h vs. 3–24 h. Safety analyses will include tabulation of the type and frequency of all adverse events and severe adverse events. All primary and secondary endpoints will be analyzed on an intention-to-treat basis (all patients will be analyzed as part of their designated treatment group) and protocol-based premise (analyses will only be performed as part of their designated treatment group when the patient received their designated treatment). For the intention-to-treat analysis, all patients who have provided written informed consent and who have been randomized in the study will be included in the analysis sample, regardless of whether they have received the correct treatment or whether there is crossover. For the protocol-based analysis, only registered patients who received the specified treatment will be included in the analysis sample. Patients who are lost to follow-up will be eliminated at the time of the last known contact. *P* values and confidence intervals will be two-sided with a significance level of 0.05.

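### Six-month CMR infarct size and EF are compared only in patients with a second scan; a two-visit model would also use the 1-week scan, for a small gain in precision and some protection against arm-specific dropout

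*Protocol article*

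**What the plan says.** CMR is scheduled twice, at 1 week and at 6 months (protocol article, Table 2). For the first scan, the Interventions and follow-up section says: "As the primary endpoint, the MSI will be measured by CMR at 1 week after PPCI". For the second: "As the key secondary endpoints, the infarct size and ejection fraction (EF) will also be measured by CMR at 6 months after PPCI". The Study endpoints section repeats "infarct size and EF measured by CMR at 6 months after PPCI" among the secondary endpoints.

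The Statistical analysis section gives one rule for all continuous variables: they "will be compared using the *t*-test or the Mann-Whitney *U* test, as appropriate". The only model it mentions concerns subgroups of the primary endpoint. On missing patients it says: "Patients who are lost to follow-up will be eliminated at the time of the last known contact". On the analysis set it says: "All primary and secondary endpoints will be analyzed on an intention-to-treat basis", and it defines that set as all consented and randomized patients.

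The Sample size calculation section raises 64 to 80 patients per arm for 20% dropout. That calculation is for MSI, the 1-week endpoint.

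**The concern.** A two-group test on 6-month values can use only patients who have a 6-month value. A patient with a 1-week scan and no second scan drops out of the comparison, although the first scan measured the same heart. The test therefore cannot deliver the stated intention-to-treat set for these endpoints.

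Two things are at stake for the endpoints meant to show a lasting effect. The confidence interval may be somewhat wider than the collected data allow. The arm difference may also be biased if patients with larger infarcts (or lower EF) miss the second scan more often in one arm than in the other. The second is possible here: the trial is open-label, and one listed reason for ending follow-up is removal by the investigators on clinical grounds.

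**Working it through.** **1. The plan's own figure.** Inputs (Sample size calculation): means 0.50 and 0.41, SDs 0.16 and 0.15, 90% power, 5% two-sided.
- Mean variance: (0.16² + 0.15²)/2 = 0.02405.
- Normal approximation: n = 2 × 0.02405 × (1.960 + 1.282)² / 0.09² ≈ 62.4, so 63 per arm.
- Noncentral t: power is 0.898 at 63 and 0.903 at 64, so 64 per arm. Then 64/0.8 = 80.

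The figure reproduces. Because MSI is measured at 1 week, 64 is the planned number with an evaluable first scan. The documents give no attrition between the two scans.

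**2. Precision.** Let n1 and n2 be the first and second scans per arm, and ρ the correlation between them (assumed). With arm-by-visit means and random loss of second scans, the variance of an arm's 6-month mean is σ²[ρ²/n1 + (1 − ρ²)/n2], against σ²/n2 for completers only. The SE ratio is √(1 − ρ²(1 − n2/n1)).

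| n1 / n2 | ρ = 0.3 | 0.5 | 0.7 | 0.8 | 0.9 |
|---|---|---|---|---|---|
| 80 / 64 | 0.991 | 0.975 | 0.950 | 0.934 | 0.915 |
| 72 / 64 | 0.995 | 0.986 | 0.972 | 0.964 | 0.954 |
| 64 / 51 | 0.991 | 0.974 | 0.949 | 0.933 | 0.914 |
| 64 / 64 | 1.000 | 1.000 | 1.000 | 1.000 | 1.000 |

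The SE falls by 0% to about 8%. At 80/64 and ρ = 0.7 the gain equals having 64/(1 − 0.49 × 0.2) ≈ 71 completers per arm instead of 64. If all dropout precedes the first scan, there is no gain.

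**3. Bias when loss depends on the first scan in one arm only.** Assume no true effect, and that in controls the odds of missing the second scan rise 2.2-fold per SD of 1-week infarct size. Numerical integration puts the mean first-scan value of control completers 0.144 SD too low at 20% missing and 0.157 SD too low at 22%. The bias at 6 months is ρ times that shift:
- ρ = 0.7: 0.7 × 0.144 = 0.10 to 0.7 × 0.157 = 0.11 SD.
- ρ = 0.9: 0.9 × 0.144 = 0.13 to 0.9 × 0.157 = 0.14 SD.
- ρ = 0.3 to 0.5: 0.04 to 0.08 SD.

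For scale, the completers-only SE with 64 per arm is √(2/64) = 0.177 SD. A bias of 0.10–0.14 SD is 0.57–0.79 SE and would raise a 5% two-sided error rate to about 9–12%.

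**4. Other mechanisms.** Simulation with 80 per arm, about 20% missing, true effect −0.3 SD at both visits, ρ = 0.7, 6,000 replicates. Where loss depends on a scan value, the odds rise by a factor of e (about 2.7) per SD.

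| Loss of second scan depends on | Bias, completers only | Bias, two-visit model |
|---|---|---|
| nothing | 0.00 | 0.00 |
| 1-week value, same rule in both arms | 0.02 | 0.00 |
| 1-week value, one arm only | 0.12 | 0.00 |
| unseen 6-month value, one arm only | 0.18 | 0.09 |

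In the last row the two-visit bias ranges from 0.14 (ρ = 0.5) to 0.04 SD (ρ = 0.9).

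**The case against.** A two-group test at 6 months is a standard analysis of a secondary endpoint, and a condensed article commonly leaves missing-data methods to the analysis plan. The elimination sentence could also be read as censoring for clinical events. This stands as a limit on the weight of the point. The point itself rests on what the article fixes: a named pair of tests for all continuous variables. Under either reading of the elimination sentence, those tests have no 6-month value to use for a patient who missed that scan.

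Four stronger readings are tempting, and the documents do not support them.
- *The planned comparison is unbiased only if missing the second scan is unrelated to infarct size.* This is too strong. With the same mechanism in both arms and no true effect, the shifts cancel; with an effect of −0.3 SD the remaining bias was about 0.02 SD.
- *The 20% dropout means that 16 patients per arm have a first scan but no second.* That allowance sizes the 1-week endpoint. A gain of zero is within the range.
- *The two-visit model removes dropout bias.* It does so only if loss depends on observed data such as the first scan. The zero in that scenario follows from the assumption.
- *Fortnightly injections make retention differ by arm.* Both arms have the same visits, injections stop at 3 months, and the article does not say that injections are clinic contacts. Differential loss is possible, not shown.

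It is also an inference that the 1-week scan yields the same quantities. MSI requires infarct size, but a 1-week EF reading by CMR is nowhere stated.

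**Conclusion.** The point holds as a modest improvement to the key secondary endpoints. As written, patients with a 1-week scan and no 6-month scan contribute nothing to the 6-month comparison of infarct size and EF, and the result is open to bias if loss depends on these measures differently by arm.

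The gain is a 0–8% smaller SE for assumed correlations of 0.3–0.9. It also removes a bias of about 0.10–0.14 SD (correlation 0.7–0.9, 20–22% missing) in the one-arm scenario, which is below one SE of the comparison. Where loss depends on the unseen 6-month value, the bias is reduced and not removed. Neither the correlation nor the attrition between scans is in the documents. The primary endpoint and the sample size are unaffected.

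**What to change.** In the Statistical analysis section, give 6-month infarct size and EF their own analysis: a repeated-measures model with the 1-week and 6-month CMR values as outcomes, arm-by-visit means and an unstructured covariance, reporting the 6-month arm contrast. With complete scans this gives the same mean difference as the planned t-test. Keep the planned t-test or Mann-Whitney test as a sensitivity analysis.

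Four details need stating.
- The 1-week value enters as an outcome and not as a covariate, because it is measured after treatment has started.
- Infarct size and EF are both read from the 1-week CMR. If EF is not, the model applies to infarct size only.
- Deaths before 6 months are handled separately, because the model would otherwise implicitly assign them 6-month values.
- A sensitivity analysis covers loss that depends on the unseen 6-month value.

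The 6-month echocardiogram in Table 2 should not carry the missing-data strategy for EF, since patients whose follow-up has ended will mostly lack it too.

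The cost is a few sentences, with no new visit or scan beyond reading EF from the 1-week images if that is not already planned. The price is an assumption that second scans are missing at random given the first.

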### Sample size calculation

Referring to our prior small sample size study, the MSI was higher in the PCSK9 inhibitor group (mean: 0.50; standard deviation [SD]: 0.16) than in the control group (mean: 0.41; SD: 0.15). To guarantee 90% power of the study at a significance level of 0.05, at least 64 patients per group will be needed. Considering a dropout rate of 20%, the required sample size is 160 (80 patients in each group). PASS 15 was used to calculate the sample size.

### Statistical analysis

Continuous variables (including the primary endpoint) will be expressed as mean (SD) or median (interquartile rage) and will be compared using the *t*-test or the Mann-Whitney *U* test, as appropriate. Categorical variables will be expressed as counts and percentages and compared using the χ2 test or Fisher's exact test, as appropriate. We plan to assess the consistency of the treatment effect on the primary endpoint among three pre-specified subgroups that will be analyzed individually and then in a multivariate model. The following subgroup analyses are planned: age: < 60 years vs. ≥60 years; sex: female vs. male; duration from symptom onset to study drug infusion: < 3 h vs. 3–24 h. Safety analyses will include tabulation of the type and frequency of all adverse events and severe adverse events. All primary and secondary endpoints will be analyzed on an intention-to-treat basis (all patients will be analyzed as part of their designated treatment group) and protocol-based premise (analyses will only be performed as part of their designated treatment group when the patient received their designated treatment). For the intention-to-treat analysis, all patients who have provided written informed consent and who have been randomized in the study will be included in the analysis sample, regardless of whether they have received the correct treatment or whether there is crossover. For the protocol-based analysis, only registered patients who received the specified treatment will be included in the analysis sample. Patients who are lost to follow-up will be eliminated at the time of the last known contact. *P* values and confidence intervals will be two-sided with a significance level of 0.05.

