Demographics/medical history	×				
Randomization	×				
Coronary angiography	×				
Fasting blood glucose	×				
Blood routine test	×	×			
Creatinine, urea nitrogen	×	×			
Electrocardiography	×	×			
CK, CK-MB, TnI/TnT	×	×			
Echocardiography	×	×			×
TC, LDL-C, TG	×	×	×	×	×
CMR		×			×
Medication		×	×	×	×
Drug side effects		×	×	×	×
MACE		×	×	×	×

CK, creatine kinase; CK-MB, creatine kinase isoenzymes; TnI/TnT, troponin I/troponin T; TC, total cholesterol; LDL-C, low-density lipoprotein cholesterol; TG, triglyceride; CMR, cardiac magnetic resonance imaging; MACE, major adverse cardiovascular event.

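### ST-segment fall time falls under the plain continuous-variable rule, which gives no value to a patient whose ST segment has not fallen (low severity)

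*Protocol article*

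**What the plan says.** The Study endpoints section of the protocol article lists "the postoperative fall time of the ST segment on ECG" as a secondary endpoint.

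The Statistical analysis section gives two comparison rules:

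- **Continuous variables.** The rule begins "Continuous variables (including the primary endpoint) will be expressed as mean (SD) or median (interquartile rage) and will be compared using the". It goes on to name two tests, Mann-Whitney U and the t-test, whichever suits the data.
- **Categorical variables.** The rule begins "Categorical variables will be expressed as counts and percentages and compared using the". It goes on to name Fisher's exact and chi-squared tests.

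A time in minutes or hours can only come under the first rule. No time-to-event method is named.

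The same section promises intention-to-treat and protocol-based analyses of all primary and secondary endpoints. For the former, "all patients who have provided written informed consent and who have been randomized in the study will be included in the analysis sample". The one sentence on incomplete data is "Patients who are lost to follow-up will be eliminated at the time of the last known contact". It does not deal with a patient who remains under observation but whose ST segment stays raised.

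**The concern.** A fall time exists only if the ST segment falls. Take three patients: one falls at 45 minutes, one at 240 minutes, and one is still raised at the last ECG. The first two contribute 45 and 240. The third has the worst result of the three and no number to contribute.

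A mean and t-test cannot include the third patient without an invented time. A Mann-Whitney test can, but only if someone decides how that patient ranks, and the article does not say. If the test is simply run on the recorded times, the comparison is confined to patients who reached ST fall. That group is selected after randomisation by the outcome itself, and treatment may change who belongs to it. A drug that brings more patients to ST fall could then show no effect, or could appear to lengthen the fall time. More frequent ECGs would not cure this, since a patient without a fall has no fall time however closely monitored.

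**Working it through.** **The plan's own figure.** The only sample size calculation is for the primary endpoint, the myocardial salvage index (MSI): means 0.50 and 0.41, SDs 0.16 and 0.15, 90% power, two-sided 0.05.

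- Pooled SD = √((0.16² + 0.15²)/2) = 0.1551.
- Normal approximation: n = 2 × (0.1551 × (1.960 + 1.282)/0.09)² = 62.4, so 63 per group.
- Exact t-test: power 0.898 at 63 and 0.903 at 64, so 64. Then 64/0.8 = 80.

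The stated 64 and 80 reproduce. They do not bear on ST fall time, for which the article gives no figures.

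**Assumptions for the check.** 80 per arm, no dropout, two-sided Mann-Whitney at 0.05. Treatment halves the non-fall share. Except where stated, fall times are log-normal with median 60 min and log-SD 0.8. None of these inputs except the 80 per arm and the test comes from the documents. Recorded times only is compared with ranking every non-faller worst.

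**Pattern 1: rescued patients fall at ordinary times.** Among patients with a recorded time the two arms have the same distribution, so the test can reject only at its type I rate. With worst ranks, the probability that a treated patient does better than a control (ties counted half) is 0.5 + (pC − pT)/2, for example 0.5 + (0.20 − 0.10)/2 = 0.55. Simulated rejection (4,000 runs):

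| Non-fall, control vs treated | Recorded times only | Worst rank |
|---|---|---|
| 10% vs 5% | 5.0% | 8.9% |
| 20% vs 10% | 5.1% | 20.4% |
| 30% vs 15% | 5.5% | 38.6% |
| 40% vs 20% | 4.4% | 60.5% |

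**Pattern 2: rescued patients fall late (median 240 min, log-SD 0.8).** The log-normal means are 60 × e^0.32 = 82.6 min and 240 × e^0.32 = 330.5 min, a gap of 247.9 min. Late fallers make up (pC/2)/(1 − pC/2) of treated patients with a recorded time. The treated mean is therefore too long by:

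- 10%: 0.05/0.95 × 247.9 = 13 min
- 20%: 0.10/0.90 × 247.9 = 28 min
- 30%: 0.15/0.85 × 247.9 = 44 min
- 40%: 0.20/0.80 × 247.9 = 62 min

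Simulated significant results in the wrong direction are about 7%, 14%, 24% and 43%. Worst ranks remove the reversal, but power is only about 5% to 21% across this range.

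**Pattern 3: treatment shortens all times, and non-fall means a time beyond a fixed window (2,000 runs).**

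| Non-fall, control vs treated | Power, recorded times only | Power, worst rank |
|---|---|---|
| 5% vs 2.5% | 0.40 | 0.48 |
| 20% vs 10% | 0.52 | 0.76 |
| 30% vs 15% | 0.54 | 0.86 |
| 40% vs 20% | 0.55 | 0.94 |

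Here the median difference has the wrong sign in only 3% to 8% of runs, and a significant reversal occurs in at most 0.1%.

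**Low non-fall.** At 5% vs 2.5%, the late-fall pattern (here late median 180 min with log-SD 0.4, ordinary times with log-SD 0.6) gives a significant reversal in about 4% of runs, against 2.5% by chance.

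**Proportion without ST fall.** For 30% vs 15%, with a pooled proportion of 0.225: z = (0.15 × √80 − 1.96 × √(2 × 0.225 × 0.775))/√(0.30 × 0.70 + 0.15 × 0.85) = (1.342 − 1.158)/0.581 = 0.32, so power is 0.62. At 20% vs 10% it is 0.42, and at 40% vs 20% it is 0.79.

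**The case against.** A reader might infer that the plan drops the worst-reperfused patients. The article does not support that. Nowhere does it say that a patient without ST fall is excluded. The intention-to-treat sentence keeps every randomised patient, and the elimination sentence covers only loss to follow-up. The conflict arises only if the stated tests are run on recorded times alone.

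Nor does the continuous-variable rule as a whole need a finite time for every patient. That is true of a mean and a t-test. A Mann-Whitney test needs only an ordering, and a median exists as long as fewer than half the patients fail to fall. A sound analysis therefore already fits within the stated rule, and the ranking convention could sit in a full protocol or analysis plan that is not shown. For the same reason, the lack of a printed definition of ST fall is not held against the article.

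The non-fall rates are assumed. A definition that nearly everyone meets would make the issue minor, and patterns 1 and 2 assume no effect in patients who would have fallen anyway.

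These objections stand, and they limit the claim. What remains is that the article does name a method for this endpoint, that one permitted version of it (mean and t-test) cannot handle non-fall, and that the intention-to-treat sentence supplies no value to use.

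**Conclusion.** The point holds as a low-severity one. The stated rule does not fit a time to an event that may not occur. Left as it is, it permits an analysis of recorded times only, which would break the intention-to-treat promise for this endpoint.

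If that analysis were done, the loss depends on the pattern. Power falls to the type I rate when rescued patients fall at ordinary times. It falls, for example, from 0.86 to 0.54 when all times shorten (30% vs 15% non-fall). Substantial reversal needs the particular pattern in which non-fall becomes late fall, so a general claim that a real benefit would reverse goes too far. All of this assumes 10% to 40% non-fall in controls, halved by treatment; near 5% little is at stake.

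The Interventions and follow-up section names infarct size and ejection fraction as the key secondary endpoints, and ST fall time is not among them. The primary endpoint and the sample size are unaffected.

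**What to change.** In the Statistical analysis section, take ST fall time out of the mean and t-test rule and choose one of two analyses in advance:

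1. Mann-Whitney test with every randomised patient without ST fall, including deaths before ST fall, given the worst rank.
2. Time from end of PPCI to ST fall, with Kaplan-Meier curves and a log-rank test. Censor patients without ST fall at their last post-PPCI ECG, and keep deaths before ST fall as not reached rather than censoring them at death.

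With either, report the proportion without ST fall by arm. In the late-fall pattern that proportion carries most of the information.

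Both options need a stated degree of fall and an observation window, if the full protocol does not already give them. In Table 2 of the article, "Electrocardiography" is marked only before operation and at 1 week, so the window cannot be read from the schedule.

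The analysis change is wording only and needs no added patients or visits. The cost is that a mean difference in minutes gives way to a rank or Kaplan-Meier summary, and that worst ranks have low power (about 5% to 21%) in the late-fall pattern. The power of the log-rank option was not calculated. The trial is open-label, so the choice should be fixed before outcome data are examined.

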### Randomization

Randomization procedures will be conducted strictly before PPCI. Eligible patients will be randomized 1:1 to the PCSK9 inhibitor group or the control group and stratified by age (≤ 60/>60; 2 categories), gender (female/male; 2 categories), time from symptom onset (< 3/3–24 h; 2 categories) using the interactive web response system (IWRS) after providing written informed consents.

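### Six-month CMR ejection fraction is compared without adjustment although a pre-PPCI echocardiogram is scheduled; the test is valid but may give up precision

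*Protocol article*

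**What the plan says.** Protocol article, Interventions and follow-up: "As the key secondary endpoints, the infarct size and ejection fraction (EF) will also be measured by CMR at 6 months after PPCI".

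Statistical analysis: one sentence covers all continuous variables, including the primary endpoint. They "will be compared using the *t*-test or the Mann-Whitney *U* test, as appropriate". No covariate is named for EF. The only model mentioned concerns the "consistency of the treatment effect on the primary endpoint among three pre-specified subgroups that will be analyzed individually and then in a multivariate model", so it does not reach EF.

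Table 2 (timetable): the row "Echocardiography" is marked in the "Before operation" column, at 1 week and at 6 months. CMR is marked only at 1 week and 6 months. Echocardiography is therefore the only cardiac imaging, apart from the angiogram, scheduled before treatment.

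Randomization: allocation is stratified by age, gender and time from symptom onset. None of these measures ventricular function.

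**The concern.** Patients reach PPCI with different ventricular function, and part of that difference is likely to persist at 6 months. An unadjusted comparison leaves that part in the residual variance, which widens the confidence interval. It also leaves any chance difference between the arms at baseline in the estimated effect. Stratification does not deal with this directly, because no stratification factor is a cardiac function measure.

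The first alirocumab injection follows PPCI, so a pre-PPCI echocardiogram cannot have been influenced by treatment and is a legitimate covariate. EF and infarct size are the two 6-month CMR endpoints, and the stated objective includes improved ventricular remodelling. The trial was sized for MSI and no power is given for EF, so efficiency matters for this endpoint.

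**Working it through.** **Inputs from the Protocol article.** Sample size calculation: MSI means 0.50 and 0.41, SDs 0.16 and 0.15, 90% power, significance level 0.05, at least 64 per group, 20% dropout, 80 per group. Statistical analysis: two-sided tests.

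**Inputs assumed.** The correlation ρ between pre-PPCI echo EF and 6-month CMR EF is not in the document; 0.1 to 0.7 is shown. The 64 evaluable patients per arm at 6 months are carried over from the MSI calculation (80 × 0.80 = 64). The 80% starting power for EF is a reference point only.

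**1. The plan's own figure.** Pooled SD = √[(0.16² + 0.15²)/2] = 0.1551. By the normal approximation, n = 2(1.960 + 1.282)² × 0.1551² / 0.09² = 62.4, so 63 per group. The exact t calculation gives 64 (power 90.3%; 63 would give 89.8%). Then 64/0.80 = 80 per group, 160 in total. The stated sample size reproduces and is not affected by this point.

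**2. Unadjusted EF comparison.** In units of the EF SD, the standard error is √(2/64) = 0.177 and the 95% CI half-width is 0.35. The effect with 80% power is (1.960 + 0.842) × 0.177 = 0.495 SD.

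**3. ANCOVA on baseline EF, complete baselines.** The variance is multiplied by 1 − ρ², so the CI width is multiplied by √(1 − ρ²). Power is recalculated for the same 0.495 SD effect.

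| ρ | Variance factor | CI narrower by | Power (80% unadjusted) | Equivalent unadjusted n per arm |
|---|---|---|---|---|
| 0.1 | 0.99 | 0.5% | 80.4% | 65 |
| 0.2 | 0.96 | 2% | 81.6% | 67 |
| 0.3 | 0.91 | 5% | 83.6% | 70 |
| 0.4 | 0.84 | 8% | 86.4% | 76 |
| 0.5 | 0.75 | 13% | 89.9% | 85 |
| 0.7 | 0.51 | 29% | 97.5% | 125 |

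**4. Missing baselines.** If a fraction m is missing at random and is filled with the overall mean plus an indicator, those patients gain no precision. The variance factor becomes 1 − (1 − m)ρ². With m = 0.30 (an assumption) and ρ = 0.5, it is 1 − 0.70 × 0.25 = 0.825. The CI is then 1 − √0.825 = 9% narrower and power is about 87%. At ρ = 0.4 the factor is 0.888 and power is about 84%.

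**5. Chance imbalance.** A baseline difference of one standard error (0.177 SD) is expected to shift the unadjusted contrast by ρ × 0.177 SD: 0.05 SD at ρ = 0.3, 0.09 SD at 0.5 and 0.12 SD at 0.7. ANCOVA removes that expected shift where the baseline is observed.

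**The case against.** The strongest case on the other side has four parts.

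- **The covariate is inferred.** Table 2 lists an echocardiogram but nowhere says that EF is recorded from it, and the endpoint's own modality has no pre-treatment scan. A reader might infer that a baseline EF is collected and then ignored; the document does not go that far. This stands, and it makes the recommendation conditional.
- **The correlation may be low.** The covariate comes from another modality, during an acute infarction and before reperfusion. This also stands. At ρ = 0.2 the gain is under 2 percentage points, and it reaches 5 points only from about 0.4 upward with complete data.
- **The planned test is sound.** A reader might infer bias or an inflated type I error. The document does not support that: under 1:1 randomisation the unadjusted comparison is unbiased on average, and its standard error already allows for chance imbalance. No power is claimed for EF, so no stated operating characteristic fails.
- **Covariates for a secondary endpoint often belong in the SAP.** This has limited force. The article does not leave the method open; it names the tests, and the proposal replaces a stated method.

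The difference in modality rules out a change score from echo to CMR. It does not rule out ANCOVA, which needs only correlation.

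**Conclusion.** The point holds as a low-cost improvement in efficiency, not as an error in the plan. The stated test is valid, and the sample size and the primary endpoint are untouched. Adjustment would narrow the EF confidence interval by about 2% at ρ = 0.2 and 13% at ρ = 0.5 with complete baselines, and by about 9% at ρ = 0.5 with 30% missing at random. It would also protect the estimate against chance imbalance in baseline function.

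This rests on EF being read from the pre-operation echocardiogram, on 64 evaluable patients per arm at 6 months, and on a correlation that the document does not supply. If the correlation is near 0.1, the gain is negligible.

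**What to change.** First confirm that EF is recorded from the pre-operation echocardiogram. If it is, take 6-month EF out of the general sentence in Statistical analysis and add, for example:

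> CMR EF at 6 months will be compared between randomised groups by ANCOVA with pre-PPCI echocardiographic EF as covariate. The adjusted mean difference with its 95% CI is the main result, and the unadjusted difference is supporting. A missing pre-PPCI EF will be set to the overall mean, with a missing-value indicator in the model.

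Do not use a change score across modalities. Do not use EF from the 1-week echocardiogram or the 1-week CMR as the covariate: both follow the first injection and could absorb part of the treatment effect.

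The cost is one or two sentences and one or two degrees of freedom (covariate and indicator), with no new visits, scans or patients. The imputation keeps every patient with a 6-month EF in the analysis without biasing the randomised comparison, but it does not recover the precision lost where the baseline is absent.
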